# LIST OF ABBREVIATIONS AND RELEVANT DEFINITIONS

| **ABR** | **General Assessment and Registration form (ABR form), the application form that is required for submission to the accredited Ethics Committee; in Dutch: Algemeen Beoordelings- en Registratieformulier (ABR-formulier)** |
| --- | --- |
| **Sponsor** | **The sponsor is the party that commissions the organisation or performance of the research, for example a pharmaceutical**  **company, academic hospital, scientific organisation or investigator. A party that provides funding for a study but does not commission it is not regarded as the sponsor, but referred to as a subsidising party.** |
| **SUSAR** | **Suspected Unexpected Serious Adverse Reaction** |
| **UAVG** | **Dutch Act on Implementation of the General Data Protection Regulation; in Dutch: Uitvoeringswet AVG** |
| **WMO** | **Medical Research Involving Human Subjects Act; in Dutch: Wet Medisch-wetenschappelijk Onderzoek met Mensen** |

# SUMMARY

**Rationale:** The daily sleep-wake rhythm is strongly disturbed in hospitalized patients. There is a lot of research on easily applicable and low-cost interventions to improve sleep. However, many of these studies have inadequate sample sizes or suboptimal study designs.

**Objective**: To evaluate the effect of implementing easy applicable and low-cost

interventions to improve sleep quality in hospitalized surgical and medical patients.

**Study design:** Cluster Randomized Controlled trial

**Study population:** Surgical and medical hospitalized patients

**Intervention**: A combination of interventions, including noise and sleep disturbance reduction, education of health-care professionals on the importance of good sleep, postponing morning check-ups for vital signs when possible, optimizing medication and iv fluid timing, reducing after-hours food intake and a “sleep menu” with items patients can choose from to improve their sleep, such as earplugs and eye-masks.

**Main study endpoint:** Sleep quality measured by the Richards-campbells sleep questionnaire.

**Nature and extent of the burden and risks associated with participation, benefit and group relatedness:** Benefits include possible improvement in sleep quality on departments where the intervention is implemented. Burden of participation is filling out a baseline questionnaire at inclusion and a short sleep diary daily for every day of hospital admission. All interventions are very low-risk.

**Key words:** sleep, hospital, multicomponent intervention

# INTRODUCTION AND RATIONAL

Our body physiology is highly intertwined with our internal human clock or circadian timing system. The human circadian timing system consists of the central clock in the hypothalamic suprachiasmatic nucleus and peripheral clocks in other brain regions and all peripheral tissues. The circadian timing system regulates circadian timing systems (i.e., rhythms of ± 24 hours) in physiology including sleep-wake behavior and attention, the secretion of various hormones such as glucocorticoids and melatonin, and the activity of the autonomic nervous system. The driving mechanism of the various clocks in the circadian timing system is the transcriptional translational feedback loop (TTFL), consisting of core clock genes with several accessory feedback loops(1-6). To synchronize the various clocks to the 24 hour rhythm of the environment, clocks respond to “Zeitgebers”, i.e. external stimuli that affect the rhythm of the molecular clock. Disruption of the circadian timing system has been shown to have a broad negative impact, including on metabolism, the immune system, mood and cognitive functioning(7, 8). We have previously shown that hospital admission and surgery disrupt the circadian timing system and reduces sleep quality(9), thereby possibly disturbing the normal homeostasis and potentially increasing the risk of morbidity and mortality. Interventions to minimize circadian disruption and improve sleep quality are therefore needed. Evidence on different easily applicable interventions to improve sleep is increasing, although well designed randomized controlled trials in the hospital setting are lacking. Interventions are usually aimed at promoting activity and reducing disturbance of the circadian timing system during the day and improving sleep at night, usually by reducing sleep disturbing factors. Interventions that are proven to be effective are eye masks(10, 11), ear plugs(12), increasing daytime- and reducing nighttime light exposure(13), nighttime noise reduction (e.g. quiet time or intervention with posters to remind nurses during rounds)(14, 15), and education of nurses on the importance of sleep(16). Several other previous studies have shown multicomponent interventions to be effective as well(17-22). However, most previous studies investigated only a single intervention at the time. All but one of the studies that investigated a multicomponent set of interventions were not set up as a randomized controlled trial. Lastly, one RCT with a multicomponent intervention was performed(21), but the set of interventions was quite limited (only eye masks, ear plugs and a white noise machine with instructions on use and encouragement to do so).

The aim of this project is to study the effect of a comprehensive set of low-cost easy applicable non-pharmacological interventions on sleep quality in hospitalized surgical and medical patients.

## Hypotheses

We hypothesize that using easy applicable low-cost interventions, we will be able to minimize disruption of the circadian timing system and improve sleep quality in hospitalized surgical and medical patients.

## OBJECTIVES

## Primary Objective:

To investigate whether a comprehensive set of low-cost and easily applicable interventions improves sleep quality in hospitalized surgical and medical patients as measured by the subjective Richard Campbell Sleep Questionnaire on the second night of admission for medical patients and first night postoperatively for surgical patients.

## Secondary Objectives:

- To investigate whether the WEsleep interventions improves subjective sleep quality for all nights of admission (max. 7)
- To investigate whether the WEsleep interventions reduced the lowering of subjective sleep quality during admission when compared to subjective sleep quality before admission (on a work-free day 30 days before admission, retrospectively assessed at inclusion)
- To investigate whether the disruption of the circadian timing system (as measured by the diurnal phase shift of midpoint of sleep) was smaller for patients in the intervention group on the first postoperative night for surgical patients and the second night of admission for medical patients
- To investigate whether the WEsleep interventions reduced night-to-night changes in subjective sleep-wake timing (i.e. midpoint of sleep, on- and offset, duration, latency, inertia and daytime napping) for all nights of admission (max. 7)
- To investigate the association between the timing of food intake (i.e. first and last meal of the day and whether food was eaten after 21:00h) and sleep quality and timing.
- For Surgical patients: To investigate the association between quality of recovery and sleep quality and sleep-wake timing
- To investigate 30-day mortality for patients admitted into intervention and control departments
- To investigate 30-day incidence of delirium for patients admitted into intervention and control departments
- For surgical patients: to investigate the 30-day incidence of surgical site infections

Objective sleep substudy

- Objective sleep substudy: to investigate the difference between intervention and control departments in objective sleep efficiency of hospitalized patients on the second night of admission (in medical patients) and the first postoperative night on ward (in surgical patients) as measured by the Dreem-3 EEG-headband
- Objective sleep substudy: to investigate whether the WEsleep interventions reduced night-to-night changes in objective sleep-wake timing (i.e. midpoint of sleep, on- and offset, duration, latency, inertia and daytime napping) for all nights of admission (max. 7)
- Objective sleep substudy: to investigate whether the WEsleep interventions influence night-to-night changes in objective sleep measures (as measured by the Dreem 3 EEG-headband and Withings Sleep analyzer) for all nights of admission (max. 7)
- Objective sleep substudy: to investigate the difference between objective sleep measures (as measured by Dreem-3 EEG-headband and Withings Sleep Analyzer) and subjective sleep measures (as measured by the Richard Campbell Sleep Questionnaire and the Consensus Sleep Diary) for a population of hospitalized medical and surgical patients
- Objective sleep substudy: to investigate the association between quality of recovery and objective sleep quality and sleep-wake timing
- Objective sleep substudy: to investigate the association between 30-day mortality and objective sleep quality and quantity
- Objective sleep substudy: to investigate the association between 30-day incidence of delirium and objective sleep quality and quantity
- Objective sleep substudy: to investigate the association between the 30-day incidence of surgical site infections and objective sleep quality and quantity (for surgical patients)

# STUDY DESIGN

In this cluster randomized controlled trial, performed in both locations of the Amsterdam University Medical Centre, we will randomize 6 surgical and 6 medical departments to either standard care group (SG) or WEsleep intervention group (WI). All adult patients admitted to the participating departments will receive the sleep improving interventions during their admission, informed consent will be obtained for sleep assessment.

Implementation of the interventions will be evaluated on a regular basis throughout the length of the study to make sure that all interventions are provided to our patients as planned. Before implementation, a baseline measurement will be conducted on all participating departments in a small number of patients (which is not part of the sample size). We observed that some interventions were gradually implemented. As such, we decided that for optimal assessment of the effect of the intervention a run-in period of 12 weeks before starting assessment of the primary and secondary outcomes would be reasonable. Sleep measurements between study onset and outcome will be used to guide implementation and will be reported in eventual journal articles.

After 12 weeks (that is, after July 1st), 33 patients per participating department will be included, for a total of 396 patients (12 departments with 33 patients each) and analyzed for the outcomes of the study. Informed consent for sleep measurements will be obtained on the first or second day of admission into one of the participating wards. Patients will be followed until discharge or for a maximum of 7 nights of admission. Patient characteristics, as well as data on the admission will be extracted from the electronic medical record. Patients will be asked to complete two questionnaires daily: Richards Campbell Sleep Questionnaire (RCSQ) on subjective sleep quality and the Consensus Sleep Diary (CSD) for day-to-day sleep wake timing. Furthermore, patients are asked at admission to complete the two questionnaires on sleep quality and sleep-wake timing on work- and work-free days (RCSQ and CSD) retrospectively, i.e. for 30 days before admission. Surgical patients will also complete a Quality of Recovery 15 (QoR-15) questionnaire twice (once at one day after surgery/first day of admission and once three days after surgery/third day of admission).

In the separate objective sleep substudy, 24 patients will be recruited from each group (medical intervention and control groups, surgical intervention and control groups), for a total of 96 patients. Measurements between April 11th and June 30th will be used to guide implementation of interventions. Patients included after July 1st will be analyzed for the outcomes of the substudy. Informed consent for the substudy will be obtained separately at the same time as consent for the main study. All patients participating in the main study will be asked to participate in the substudy as well. After obtaining consent, a lottery system will decide which patients can participate in the substudy (due to the scarcity of available Dreem-3 EEG headbands and Withings Sleep Analyzers).

In the substudy, objective sleep in patients will be measured with the Dreem-3 EEG-headband and the Withings Sleep Analyzer. The Dreem-3 headband uses electro-encephalography (EEG) and a validated algorithm to differentiate between wakefulness and various sleep stages (Rapid-Eye Movement (REM)-sleep and non-REM N1, N2 and N3 sleep) and the time at which these occur. The Withings Sleep Analyzer can be placed under the mattress and uses measurement of movement to differentiate between wakefulness and light, deep and REM-sleep and the times at which these occur.

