## Inclusion criteria

In order to be eligible to participate in data collection for this study, a subject must meet all of the following criteria:

A) (elective surgery patients)

- Adult (18+) patients
- Undergoing elective non-cardiac surgery with planned (postoperative) overnight stay
- Willing and able to provide informed consent
- Able to read and write in Dutch

B) (medical patients)

- Adult (18+) patients on medical departments with expected stay of at least two nights.
- Willing and able to provide informed consent
- Able to read and write in Dutch

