## Randomization

As this is a cluster randomized controlled trial, patients will not be randomized individually. 12 departments will be asked to participate in the trial (6 medical and 6 surgical departments. Medical and surgical departments will be randomized separately, using a standard method of randomization (e.g. randomization.com). This will yield 3 medical en 3 surgical departments in both groups (intervention vs. control). The Intensive Care Unit and the surgical department for Cardiothoracic Surgery will be excluded from randomization. Inclusion of departments will stop when 6 medical and 6 surgical departments are found that are willing to participate.
3 medical and 3 surgical departments will provide care using the WEsleep-protocol from the start of the trial. The other departments will provide standard care during this time.

After the study, we will also implement the interventions at the control departments, as long as the preliminary results are positive.

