### Time of main endpoint

Main endpoint will be measured on the second night of admission for medical patients, first night after surgery for surgical patients.

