## Randomisation, blinding and treatment allocation

After inclusion in the trial, departments will be randomised by an investigator through online software (e.g. randomization.com) and according to Good Clinical Practice guidelines.

All patients admitted into one of the randomized departments is eligible to participate in the study, provided that the inclusion criteria are met.

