### Screening and inclusion

Patients will be screened for eligibility by checking patient records of patients admitted into each of the participating departments. Patients that have objected to participating in medical studies will not be approached or screened for eligibility, to comply with AVG requirements.

Patients eligible will be approached at the department they are admitted at and will be included after informed consent has been obtained.

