## Recruitment and consent

Patients admitted into one of the participating departments who meet inclusion criteria will be asked if they are willing to participate in the evaluation of the intervention at the first day of hospital admission (or as soon as possible, if recruitment cannot take place on the first day (e.g. admission in the weekend)). Patients will be recruited after informed consent has been obtained.

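### The consent window can run past the primary outcome night, so some patients could decide to take part already knowing how they slept

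*Protocol*

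**What the plan says.** On consent, the Protocol's Study design section states: "Informed consent for sleep measurements will be obtained on the first or second day of admission into one of the participating wards". Section 11.2 (Recruitment and consent) gives a different window: the first day, or "as soon as possible, if recruitment cannot take place on the first day". Weekend admission is its example, and it sets no latest time.

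On the outcome, Time of main endpoint states: "Main endpoint will be measured on the second night of admission for medical patients, first night after surgery for surgical patients". The surgical inclusion criterion is "Undergoing elective non-cardiac surgery with planned (postoperative) overnight stay". It does not require a night on the ward before the operation.

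On the order of events, section 10 (Statistical analysis) keeps every patient who has a total RCSQ score for the primary night, and drop-outs are replaced. The home RCSQ and CSD are requested at admission according to Study design, but at inclusion according to the secondary objectives and endpoints. The Randomization section says that "3 medical and 3 surgical departments will provide care using the WEsleep-protocol from the start of the trial". Outcome patients are enrolled only after the 12-week run-in. Under Screening and inclusion, "Patients eligible will be approached at the department they are admitted at and will be included after informed consent has been obtained". The section whose heading includes blinding describes none.

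**The concern.** In a cluster trial that recruits patients after the clusters are allocated, randomisation balances departments. It does not control which patients in a department agree to be measured. That is usually tolerable if patients decide before the outcome occurs. If they are asked after the primary night, the decision to take part can depend on the outcome itself: someone who slept badly may be less willing to fill in sleep questionnaires, or more willing. Covariate adjustment cannot be relied on to undo selection on the outcome.

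The home RCSQ and CSD have a related problem. If they are completed at a late inclusion, the reference for the home-versus-hospital comparison and for the phase shift is recalled after exposure to the ward and, in intervention departments, to the sleep brochure.

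**Working it through.** **Timing, surgical patients.** Take surgery on the day of admission, which the inclusion criteria allow. The first postoperative night is then night 1. Consent on day 2 is within the Study design window and comes after that night. If the patient is admitted the day before surgery, the primary night is night 2 and day-2 consent precedes it.

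**Timing, medical patients (198 of 396).** The primary night is night 2, so consent on day 1 or 2 precedes it. The Study design sentence alone causes no problem here. Under section 11.2, a patient admitted on Saturday (day 1) and first reached on Monday (day 3) consents after night 2, which ran from Sunday to Monday. Day 3 also lies outside the Study design window, so the two passages disagree.

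**What happens next.** The RCSQ is a next-day rating, so a patient who consents on the morning after can still supply a score. Nothing bars this, and with a score the patient meets the section 10 analysis rule.

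**The plan's own figure.** Inputs from the sample size section: SD 10.27, ICC 0.030, 3 clusters of 33 per arm, difference 7.7, two-sided 0.05, degrees of freedom from clusters (6 - 2 = 4).
- Design effect = 1 + (33 - 1) × 0.030 = 1.96
- SE = 10.27 × √(2 × 1.96 / 99) = 2.044
- Power (noncentral t, 4 df) = 80.1%, which reproduces the stated 80%.

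This point disputes no stated figure.

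**Illustration of size (assumed inputs).** The protocol gives neither the share reached late nor the strength of any selection. Assume no true effect and selection in one arm only. A share f of patients is approached after the primary night; of these, the worst-sleeping fraction q is not included and is replaced.
- Mean shift among late patients who are included = 10.27 × φ(z_q)/(1 - q) = 2.00, 3.59 and 5.10 points for q = 10%, 20% and 30%
- Late share among those included = f(1 - q)/(1 - fq)
- Spurious difference = late share × mean shift

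Example, f = 50% and q = 30%: 0.35/0.85 = 0.412, and 0.412 × 5.10 = 2.10 points, or 2.10/7.7 = 27% of the target.

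| f | q = 10% | q = 20% | q = 30% | False-positive risk |
|---|---|---|---|---|
| 10% | 0.18 | 0.29 | 0.37 | 5.1–5.2% |
| 25% | 0.46 | 0.76 | 0.97 | 5.4–6.6% |
| 50% | 0.95 | 1.60 | 2.10 | 6.5–12.6% |

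The last column uses the 4-df cluster test of the sample size section, for 99 against 99 patients, at nominal 5%. With equal selection in both arms the spurious difference is zero, although the population measured is still a selected one.

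**The case against.** The strongest reply is that the plan is evidently meant to be prospective. Questionnaires are handed out after consent, and Study design places the home questionnaires at admission. Substudy consent is taken together with main-study consent, and its EEG outcome falls on the same primary night; a headband cannot be worn for a night already past. One can also read Study design as capping section 11.2 at day 2, which removes the medical route. This shows intent, and it stands as such. It is not a rule, and it does not help the same-day surgical patient, for whom day 2 is expressly allowed.

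Two stronger readings are tempting and are not supported.
- A reader might infer that recruiters know the allocation and choose whom to approach. The protocol does not say who takes consent, what they know, or that they pick among eligible patients; section 11.2 reads as asking those who qualify. Knowledge of allocation is a reasonable inference from an unblinded, ward-level intervention with posters on display, but it remains an inference.
- A reader might infer a larger bias by supposing that everyone below the median declines in one arm. With 20% of included patients late, that gives 0.2 × 0.798 × 10.27 = 1.64 points (21% of 7.7). This is a one-arm worst case. If instead 20% are approached late and half of those decline and are replaced, the late share is 0.1/0.9 = 11%, and the shift is 0.111 × 0.798 × 10.27 = 0.91 points (12%).

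**Conclusion.** The point holds in a limited form. The protocol allows consent after the primary night for surgical patients operated on the day of admission. Through the open-ended wording of section 11.2, it also allows it for medical patients reached late. Nothing removes such patients from the 33 or from the analysis. Inclusion that depends on the outcome is therefore possible; the documents do not show that it occurred or that it differed between arms.

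The size is unknown. The range of about 0.2 to 2.1 points rests on three assumptions: 10–50% of one arm approached late, the worst-sleeping 10–30% of those lost, and no such loss in the other arm. For late shares of 10–25% it is at most about 1.0 point. More patients per department would not remove such a bias. The issue merits correction because it touches the primary outcome and is cheap to close, not because serious bias has been demonstrated.

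**What to change.** - Reconcile Study design and section 11.2 so that they give one consent window.
- State that consent and the home RCSQ and CSD must be completed before the primary outcome night, and that patients first reached later do not count towards the 33.
- Record the time of consent relative to that night for every patient.
- The note under the exclusion criteria shows that inclusion had already begun. Apply the rule from a dated amendment, and for patients already included add a sensitivity analysis restricted to those who consented before the primary night.

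A consecutive or random approach order and a screening log by department would be useful additions but are not essential to this point.

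The cost is a protocol amendment, the loss of some same-day surgical and weekend admissions who are reached late, and slightly slower filling of 33 per department. Patients recruited before and after the amendment may differ a little, which the recorded consent times will help to show.
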